### Concealment mechanism {16b}

Once the consent form is received, a computer-generated random number from 1 to 210 will be assigned to that participant. Each number from 1 to 210 will be assigned a random group type: PD intervention, PD control, or HC. HCs can only be assigned numbers assigned an HC group type. For the numbers randomly allotted for PD participants, the computer-generated random number assignment will be set such that results in a 1:1 ratio, stratified by gender and PD staged I and staged II determined by the Hoehn and Yahr scale. The participant’s number will become the identifier for the participant’s collected data for data analysis. Once all participants have been enrolled and assigned, the list of which participants were distributed among the groups will be kept in an opaque, sealed envelope. Upon completion of consent, randomization, and baseline data collection, the participant will receive an opaque and sealed envelope, associated with their randomized number. The package will provide further at-home instructions as a physical copy, contact information for additional questions, and how to access a digital copy of their assigned group’s instructions. Verbal instructions, additional resources, and training for at-home tasks will be provided to participants and caregivers. Access to video instructions for at-home tasks is also provided as a supplement.

### Implementation {16c}

BZ and ZL will generate the allocation sequence and prepare the opaque envelopes with further instructions. LP will enroll participants, allocate participants, train participants and their caregivers for at-home tasks, and provide additional support to participants, accessible through phone calls, to ensure adherence.

## Assignment of interventions: blinding

### Who will be blinded {17a}

Primary investigators will be blinded to the data collected.

### Procedure for unblinding if needed {17b}

Not applicable to study; unblinding will not be utilized.

## Data collection and management

### Plans for assessment and collection of outcomes {18a}

Neuroimaging assessment: Functional near-infrared spectroscopy (fNIRS) will be employed to examine the cortical neural activity changes from the SFT intervention. The probe of the continuous wave system (ETG-4000, Hitachi Medical Co., Japan) will be used to measure changes in oxygenated (HbO_2_) and deoxygenated (HbR) hemoglobin [35, 36].

The 52-channel probe set will be placed on the prefrontal, premotor, and supplementary motor areas guided by the nerve navigation system and international 10–20 system for electrocochleography. The CZ and FZ positions from the 10–20 system are first identified. The central sulcus through CZ will be marked with a line and a second line, parallel to the first, will run through FZ. A third line, parallel and at the mid-point between the first two marks, will be used to align the midline of emitters-detectors. There are 20 emitters, set at 690 nm and 830 nm, respectively, and 16 detectors in the fNIRS head band, and will be used in a 52-channel configuration with each channel sampled at 10 Hz. The separation between each emitter and detector pair will be 3 cm [37, 38].

fNIRS will be taken at baseline, week 4, week 8 (end) and week 12 (follow-up) during motor-timing control assessments. Neuroimaging will be conducted for both the control and intervention arms. The data collected from this assessment is recorded digitally and uploaded to a designated cloud server immediately after assessment.

#### Motor-timing control assessment

A synchronous finger tapping assessment task will be used to measure participant’s motor-timing control. During the assessment fNIRS will be used to measure cortical neural activity. Participants will sit in front of a computer screen and asked to tap the “1” key, on the number pad of a standard QWERTY keyboard, as soon as the visual cue, a white star on a black background “ ” appears on the screen. This visual cue will appear for set durations. This duration will be 500 ms initially and will be adjusted based on the feedbacks from the subjects. SFT performance is scored by measuring the delay time between the cue for tapping and the recorded keystroke delivered by the participant. Delivery of the assessment and data collection will be facilitated by E-Prime 3.0, a computerized environment for psychological types of experimental design, data collection, and analysis. The performance in this assessment is recorded digitally and uploaded to a designated cloud server immediately after assessment.

The participants will be seated in a quiet room in front of a computer monitor. The fNIRS system and earphones will be fitted onto the participants and the audio’s volume will be adjusted to a comfortable level. Prior to assessment, the participants will be read instructions and perform a training module to ensure participants understand and know what to expect. Participants will be asked to relax and to restrict their motor motions before the start of the experimental paradigm. Subjects rest for the first 20 s to provide a fNIRS baseline signal correction. The participant will then be asked to complete the following tasks 3 times with 120 s break in between each 170 s set of the following:
Synchronous finger tapping (SFT): Subjects must tap right index finger as a visual cue appears. The visual cue will appear 10 times at the rate of 1000 ms, 1500 ms, and 2000 ms, respectively for every cycle. The number of times and rate the visual cue appear will be adjusted if no significant difference in learning is observed between patients with PD and healthy subjects.Continuous finger tapping (CFT): Subjects are asked to tap their right index finger such that it maintains the previous temporal rhythm.Rest: participants are asked to restrict their body movements (Fig. 3).

**Fig. 3 Fig3:**

Schematic of experimental paradigm. BR, baseline rest; SFT, synchronous finger tapping; CFT, continuous finger tapping. In the SFT task, visual stimuli will appear at three different rates 1000 ms, 1500 ms, and 2000 ms respectively

Three neuropsychological assessments will be employed for measuring the therapeutic effects of the music therapy on the disease. The Unified Parkinson’s Disease Rating Scale (UPDRS), n-back task, and Montreal Cognitive Assessment (MoCA) will also be measured at baseline, 4, 8, and 12 weeks.

Three neuropsychological assessments will be employed for measuring the therapeutic effects of the music therapy on the disease. The Unified Parkinson’s Disease Rating Scale (UPDRS), n-back task, and Montreal Cognitive Assessment (MoCA) will also be measured at baseline, 4, 8, and 12 weeks.

#### UPDRS

The UPDRS objectively assesses the severity of PD based off the disease’s burden on the individual and can describe disease progression and treatment response. A total of 42 ratings are split between multiple categories. Examples of categories measured include mental impairments (mood and intelligence), activities in daily living (speech, salivation, level of independence to perform normal tasks such as turning in bed), motor skills (facial, tremor severity in extremities, rigidity), and other complications. Each category has a 0–4 rating determined by the examiner and summed, where a higher score reflects greater disability (maxed at 195 points) [39]. The performance in this assessment is recorded digitally and uploaded to a designated cloud server immediately after assessment. If paper copies are used, then the document will be scanned and a digital copy with manual inputs will be made.

#### N-back task

The n-back task examines an individual’s working memory and working memory capacity by employing a visuo-spatial continuous performance task. The task used in this study was based on the n-back tasks from Beato et al. [40]. This study will employ 3-back tasks that are delivered digitally and started with a digital countdown. The participant is asked to input a keystroke on standard QWERTY keyboard with their right-hand to indicate whether a target visual stimulus presented on the screen was identical to a previously shown stimulus presented “n” trials ago. The stimulus will be a white square randomized into one of six positions on a black screen. The first cue stimulus will be presented on the screen for 3 s and the individual has 3 s to respond with a “1” keystroke to indicate “same” or a “2” keystroke to indicate “different.” A new stimulus will appear after a 1-s inter-stimulus interval. Each task will include responses to two sets of 15 and thus each assessment will last approximately 10 min. The performance in this assessment is recorded digitally and uploaded to a designated cloud server immediately after assessment.

#### MoCA

MoCA assesses for an individual’s cognitive abilities via a one-page, 30-point exam, delivered as a 10-min assessment. This includes orientation (6 points), concentration and attention (6 points), executive functions (3 points), memory (5 points), conceptual thinking (2 points), language (3 points), and visuo-constructional skills (5 points) [41]. The Chinese (Mandarin) MoCA readily available from mocatest.org will be utilized throughout this study [42]. The performance in this assessment is recorded digitally and uploaded to a designated cloud server immediately after assessment. If paper copies are used, then the document will be scanned and a digital copy with manual inputs will be made.

### Plans to promote participant retention and complete follow-up {18b}

Participants and participant family members will be given a reminder (via e-mail and phone call) a week before to schedule the follow-up.

### Data management {19}

All participant data will be identified as their trial identification number assigned during allocation. Each trial identification number will have their own designated folders. Data collected from fNIRS, motor control assessment, and N-back tests are conducted on a single laptop and will be automatically uploaded to their respective designated cloud storage databases immediately after each individual measurement. UPDRS and MoCA assessments will be recorded digitally using a digital copy of the assessments and saved into their respective participant folders. If paper copies are used, then the physical copies will be scanned and manually converted to a digital copy after the assessment. Any physical copies collected throughout the study will be stored for up to 5 years. A master datasheet that collects all digital data scores and is organized by participant number and time point will be pre-programmed to conduct range checks for all data values collected.

Video and audio recorded from participant phones or cameras will be uploaded onto the same database but stored separately from the data collected from assessments such that it is not accessible by data analysts or primary investigators. Only research assistants who are designated to transfer the files into the cloud storage or are trained to score the videos have access to the video and audio files.

### Confidentiality {27}

Confidentiality is not an issue in the data collecting country; however, the data will be stored on the cloud server provided by the hospital which is already secured to ensure strict access. Only primary researchers who are enrolling participants, collecting or analyzing data and other principal members of the research team will be able to access the cloud database. Before the data is uploaded to the cloud, it will be organized based on trial identification number instead of group and individuals’ names. Access to the database may be granted upon request from other researchers, study entities, or miscellaneous government associated groups who wish to conduct prospective meta-analyses. For international entities that request for data access, video recordings are pre-processed to de-identify the participants.

### Plans for collection, laboratory evaluation, and storage of biological specimens for genetic or molecular analysis in this trial/future use {33}

Not applicable to study; no biological specimens collected.

## Statistical methods

### Statistical methods for primary and secondary outcomes {20a}

Data analysis will commence after all retained recruited participants have completed their 12-week assessment.

#### Finger tapping performances and neuropsychological assessments

The SFT and CFT performances as well as neuropsychological measurements collected from the three groups (intervention and control arms) during assessment will be compared using a two-sample *t* test. Correlative data and the extent of the intervention’s effect on finger tapping performances and PD symptoms may be extrapolated from this data.

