**Methods:**

For patients suffering from Parkinson’s disease (PD), we propose a daily 25-min music-based synchronous finger tapping (SFT) intervention for 8 weeks. Eligible participants with PD are split into two groups: an intervention group and a control arm. In addition, a third cohort of healthy controls will be recruited. Assessment of finger tapping performances, the Unified Parkinson’s Disease Rating Scale (UPDRS), an n-back test, the Montreal Cognitive Assessment (MoCA), as well as oxygenated hemoglobin (HbO_2_), deoxygenated hemoglobin (HbR), and total hemoglobin activation collected by functional near-infrared spectroscopy (fNIRS) are measured at baseline, week 4 (during), week 8 (post), and week 12 (retention) of the study. Data collected from the two PD groups are compared to baseline performances from healthy controls.

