### Sample size {14}

For this study, a total 210 participants (70 participants in three groups with a 10% attrition rate), are recruited over an 18-month period. We aim to recruit an even distribution of age, PD staged I, and II as determined by the Hoehn and Yahr scale, and gender to maximize statistical significance. This study is an exploratory prospective randomized controlled study with the primary outcome being the HbO_2_ value measured by fNIRS. Because there are no pilot study nor previous studies identical to this, the sample size was calculated by using power calculations (where *α* = 0.05, *β* = 80%, and we assume a conservative average difference between the PD groups). Klempir et al.’s study was used to estimate the baseline averages of HbO_2_ changes; however, there are notable inherent differences between this protocol and the referenced study. Klempir et al. describes HbO_2_ changes between participants with and without DBS during a finger tapping exercise [34]. Although our study may involve participants who use DBS as a treatment, we are not examining how various forms of treatment (pharmaceutical or DBS) affect motor control. Thus, the estimated HbO_2_ baselines when DBS is ON from Klempir’s study were approximations of the PD control group’s performance.

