### Recruitment {15}

Potential participants are recruited from the First Affiliated Hospital of Dalian Medical University. Recruitment will be managed by BZ and ZL. Participants’ spouses are also invited to participate as healthy controls if they meet the inclusion criteria. We will assume a conservative estimate of 10% attrition due to various reasons such as voluntary withdrawal, illnesses during studies, and other uncontrolled factors.

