## Assignment of interventions: allocation

### Sequence generation {16a}

Participants with PD are sorted into and then randomized into the intervention or control groups in a 1:1 balanced ratio stratified by gender and PD staged I and staged II as determined by the Hoehn and Yahr scale. Allocation into randomized study groups are conducted via a computer-generated random number table and determined during the pre-study procedures during allocation when informed consent and baseline measurements are made. The number generation is facilitated by R3.6.3, a computer random number generator typically used by the Scientific Research Department of the hospital. Participant groups are not known to clinical investigators, site personnel, nor data analyzers.

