#### fNIRS data

An initial band pass filter will be applied to the raw fNIRS data before further processing to remove noise and drifts. Neuroactivity in various regions of interest including, prefrontal, pre-motor, supplementary, and primary cortex, will be analyzed by constructing a general linear model for each subject then estimating parameters and obtaining contrast values of the total oxy-Hb and deoxy-Hb signals. The contrast value images can be averaged within groups and a group analysis can be done using a *t* test. The averaged signal levels of each group will be plotted on a time vs total blood flow graph and compared to determine intervention effect.

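### The named two-sample t test does not fit three groups at four visits and leaves baseline and the stratification factors out of the randomised comparison; the fNIRS plot should not decide the effect

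*Protocol article*

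**What the plan says.** **Tapping and neuropsychological outcomes.** Under Finger tapping performances and neuropsychological assessments, the Protocol article says that data "collected from the three groups (intervention and control arms) during assessment will be compared using a two-sample" t test. It does not say which pair of groups, which visit, or whether raw or change values enter the test. It names no covariate.

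**Design.** The abstract and the Objectives give measurements at baseline and at weeks 4, 8 and 12. Sequence generation {16a} randomises the PD participants 1:1, "stratified by gender and PD staged I and staged II as determined by the Hoehn and Yahr scale". The healthy controls are a separate, non-randomised group.

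**Outcomes.** Outcomes {12} frames most outcomes as preservation or improvement from baseline, and the imaging outcome as a reduction of prefrontal HbO2 from baseline. It says outcomes are determined from differences between the visits and by comparison with the control arms.

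**fNIRS.** The fNIRS data section plans a general linear model per subject, with contrast values for the oxy-Hb and deoxy-Hb signals. In permissive wording, it then allows a group t test. The next sentence is definite: the "averaged signal levels of each group will be plotted on a time vs total blood flow graph and compared to determine intervention effect".

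**Strata in the analysis.** Methods for additional analyses {20b} mentions gender, age and disease stage only as interacting factors that might be explored further.

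**The concern.** The article does more than leave detail open: it fixes a method, and that method does not match the data structure. A two-sample t test cannot take three groups or four visits at once. Used as written, it becomes an unspecified set of pairwise, visit-by-visit tests.

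For the randomised contrast, PD intervention against PD control, two kinds of information already being collected are left out of the model:

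- **Baseline value.** Every outcome is measured at baseline. If the test is on raw follow-up values, chance baseline imbalance passes into the estimate. If it is on change scores, baseline is subtracted with a fixed weight of one, which adds noise when the correlation is low.
- **Stratification factors.** Randomising within gender and stage and then ignoring both in the analysis gives standard errors that are too large whenever those factors predict the outcome.

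For fNIRS, which Sample size {14} treats as the primary outcome, one sentence makes a comparison of plotted curves a basis for judging the effect. The plotted quantity is total blood flow, not the prefrontal HbO2 change in Outcomes {12}. A comparison of curves has no confidence interval and no error rate.

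**Working it through.** **Inputs from the article.** Sample size {14} gives "a total 210 participants (70 participants in three groups with a 10% attrition rate"). Recruitment {15} adds: "We will assume a conservative estimate of 10% attrition". So 70 × 0.9 = 63 evaluable per arm. Alpha is 0.05, taken here as two-sided. The 80% printed as beta is read as power.

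**Inputs the article does not give.** It states no difference, no SD and no baseline to follow-up correlation. I assume a standardised difference d = 0.5 and correlations rho of 0.3, 0.5 and 0.7.

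**Can the plan's own figure be reproduced?** Not from its stated inputs, because the effect size is missing. Back-solving by the normal approximation:

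- detectable d = (1.960 + 0.842) × √(2/63) = 0.499
- with d = 0.5, n = 2 × (1.960 + 0.842)² / 0.5² = 62.8, rounded up to 63, and 63/0.9 = 70

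So 70 per group is consistent with an unadjusted comparison of two groups at one time with d = 0.5. This only makes 0.5 a reasonable illustrative value; it does not show that the sponsor used it.

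**Power of three analyses of the two PD arms at one follow-up visit.** Noncentral t, 124 degrees of freedom, noncentrality = d × √(63/2) / √f, where f is the variance relative to the follow-up t test:

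- follow-up t test: f = 1, noncentrality 0.5 × 5.612 = 2.806, power 79.5%
- change-score t test: f = 2(1 − rho)
- ANCOVA on baseline: f = 1 − rho²

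| rho | f, change | f, ANCOVA | Follow-up t test | Change-score t test | ANCOVA |
|---|---|---|---|---|---|
| 0.3 | 1.40 | 0.91 | 79.5% | 65.3% | 83.1% |
| 0.5 | 1.00 | 0.75 | 79.5% | 79.5% | 89.5% |
| 0.7 | 0.60 | 0.51 | 79.5% | 94.9% | 97.4% |

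**Reading the table.** Against a follow-up t test, ANCOVA gains about 4, 10 and 18 points. Against a change-score t test, the gain is about 18, 10 and 2.5 points. The two patterns run in opposite directions, so the size of the loss depends on which t test is meant, and the article does not say. The direction does not: 1 − rho² is below 1 for any non-zero rho, and it is below 2(1 − rho) for any rho below 1, because 2(1 − rho) − (1 − rho²) = (1 − rho)².

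**Stratification factors.** No figure can be given, because the article does not say how strongly gender and stage predict each outcome.

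**fNIRS sentences side by side.** The model and t test work on each subject's contrast values and can give an estimate and a p value. The plot works on group-average total blood flow over time. Only the plot sentence refers to determining the intervention effect, and its wording is definite where that for the t test is permissive.

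**The case against.** Several stronger readings are tempting, and the document does not support them.

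- **That fNIRS is judged by a plot alone.** It is not. The same section plans a per-subject model and a group t test. What remains is that the plot is also given an inferential role, on a quantity that is not the stated outcome.
- **That baseline is ignored.** Outcomes {12} speaks of differences from the pre-measurement, so change scores may be intended. On that reading baseline imbalance does not simply carry over into the estimate. What remains is that baseline is not used as a covariate, and the change score never beats ANCOVA in the table.
- **That the strata are absent.** They appear under additional analyses, but only as optional exploration of interactions. That does not put them in the main comparison.
- **That comparing PD visits with healthy-control baselines spoils the result.** The abstract does say: "Data collected from the two PD groups are compared to baseline performances from healthy controls". But the healthy controls are a non-randomised benchmark. The treatment effect rests on the two PD arms, which share one assessment schedule, so this is a separate matter and no part of the present point.

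It can also be said that this is a condensed article on an exploratory trial, and that the pair, visit and covariates usually go into an analysis plan. That is fair for the unstated details and they are not the complaint. It does not cover the test that is named. Nor is a mixed model the only remedy: ANCOVA at one visit would recover the baseline gain.

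**Conclusion.** The point holds in this form: the named t test does not fit three groups and four visits, and it leaves baseline as a covariate and the stratification factors out of the randomised contrast. The fNIRS section, beside a usable model and t test, lets a total blood flow plot bear on the effect.

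Under the assumed d = 0.5 with 63 per arm, the power forgone against ANCOVA ranges from about 2.5 to 18 points, depending on rho and on whether raw or change values are tested. These figures are illustrative because d and rho are assumptions. That adjustment lowers variance is not in doubt for any outcome correlated with its baseline.

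A reader might infer that the trial's comparison would be invalid. It would not: an unadjusted comparison of randomised arms remains valid. The fault is inefficiency and a poor match to the design, so the change is recommended and not essential.

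**What to change.** For PD intervention against PD control, replace the two-sample t test with a baseline-adjusted model for each continuous outcome. Either of these would serve:

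1. ANCOVA at one prespecified visit, with baseline value, gender and Hoehn and Yahr stage as covariates.
2. A mixed model for repeated measures on weeks 4, 8 and 12, with baseline value, gender, stage, visit, arm and arm-by-visit terms, and one visit named in advance for the main estimate.

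Report the arm difference with its 95% confidence interval. Analyse each subject's prefrontal HbO2 contrast in the same model, and say that the time-course plot is descriptive. Keep comparisons with healthy controls apart from the treatment effect.

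The cost is a few sentences in the protocol or analysis plan and a few lines of code. All the variables are already collected. Analysis is not due until every retained participant has completed week 12, so the change needs no alteration to trial conduct if it is fixed before the data are examined.

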### Eligibility criteria {10}

Potential participants will be recruited from the Neurology Department of the First Affiliated Hospital of Dalian Medical University in China. Only individuals who meet the inclusion criteria will be invited to participate in the study.

There will be two populations participating in this study: one will be patients diagnosed with PD with intervention and the other without. A group of healthy participants will be recruited to serve as healthy controls (HC) that will provide the baseline assessment data to gage the severity of PDs in the patient populations.

The following are the inclusion criteria for participants with PD recruitment:
Aged 40–80 years old, both genders, and right-handed;Clinical diagnosis of idiopathic PD according to the 2015 Movement Disorder Society (MDS) Clinical Diagnostic Criteria for Parkinson’s Disease;Rated as stage I to II on the Hoehn and Yahr scale;Score greater than 21 points on the Montreal Cognitive Assessment (MoCA);Maintain a stable dosing of anti-PD or deep-brain stimulation (DBS) treatment throughout the duration of the study;Able to travel to and participate in the data collection process.

Exclusion criteria for participants with PD recruitments include:
Individuals who do not meet the inclusion criteria;Presence of significant hearing impairments;Extensive previous musical training;A history of any other neurological condition (i.e., Alzheimer’s disease, epilepsy, stroke) or psychiatric disorders (i.e., major depression, psychoses).

The HC group will consist of subjects recruited from hospital staff and students as well as students and faculty members from Dalian University of Technology. In addition, participants’ spouses will also be invited to participate. The HC group must have the following qualities to be included:
Aged 40–80 years older, both genders, and right-handed.

HC will be excluded along the same criteria that was established for the PD recruitment.

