## Interventions

### Explanation for the choice of comparators {6b}

The PD intervention group is compared with the PD control group and a healthy control (HC) group. The PD control group is composed of participants diagnosed with PD and who meet the inclusion criteria. This PD control group is instructed to maintain the participants’ prescribed medication and care documented at the time of baseline assessment including any form of deep brain stimulation, if applicable. Any deviation from what was recorded at the time of taking baseline assessments are recorded during assessments and included when analyzing the data.

The second control group, the HCs, is composed of participants who meet the HC group inclusion criteria. This group predominantly consists of healthy spouses of the PD participants and individuals who share similar demographics to the participants diagnosed with PD. Measurements from the HCs are necessary because they serve as a normal, non-pathological benchmark, which has not been recorded before with this specific demographic and type of study paradigm. Furthermore, since spouses typically have similar lifestyles as their partners the measurements taken may help reduce the uncontrollable deviations due to dietary habits, living conditions, and environmental factors. HCs are asked to continue normal routine and must report any major deviations from baseline assessment routine (e.g., new medication to treat non-neurological illnesses that may affect motor movement or major injuries like head trauma). These deviations are noted for data analysis.

The neuronal activities of generating motor movement or processing a rhythmic external cue each should separately elicit measurable neuronal activation. However, when combined, a sensorimotor integration effect occurs such that motor movement is the result of a rhythmic external cue. Thus, the use of the HC and PD controls is to examine how movement coupled with an external sensory cue (a rhythmic auditory stimulus and in this study, music with rich rhythmic contents) impacts motor synchronization and control in PD.

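### Some healthy controls are spouses of PD participants, but the PD-versus-healthy comparisons of tapping and neuropsychological outcomes use a two-sample t test that assumes independent groups

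*Protocol article*

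**What the plan says.** The section on the choice of comparators {6b} describes the healthy controls: "This group predominantly consists of healthy spouses of the PD participants and individuals who share similar demographics to the participants diagnosed with PD". It gives a reason for using spouses: "since spouses typically have similar lifestyles as their partners the measurements taken may help reduce the uncontrollable deviations" that arise from diet, living conditions and environment.

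The eligibility section {10} puts the weight elsewhere. There, "The HC group will consist of subjects recruited from hospital staff and students", together with students and faculty of a university, and participants' "spouses will also be invited to participate" as a further source. Recruitment {15} likewise treats spouses as an additional invitation. No section states how many healthy controls will be spouses.

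The abstract plans to compare data from both PD groups with the healthy controls' baseline performance. For tapping and neuropsychological measures, Statistical methods {20a} says that data "collected from the three groups (intervention and control arms) during assessment will be compared using a two-sample" t test. For fNIRS it says only that "The contrast value images can be averaged within groups and a group analysis can be done using a" t test, without saying which kind. No couple or household term appears. The possible further factors in {20b} are gender, age and disease stage.

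**The concern.** A spouse control and the PD participant to whom that control is married are a linked pair. If partners resemble each other, as the comparator section supposes, their outcomes covary. A two-sample t test sets that covariance to zero, so its standard error does not match the recruitment described.

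The direction depends on the sign of the correlation. If it is positive, the standard error is too large, the test is conservative and power is lost. If it is negative, which is possible on a sex-dependent measure since most couples are of opposite sex, the standard error is too small and the test rejects too often.

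What is at stake is the PD-versus-healthy benchmark, which the abstract, the trial design and the comparator section all rely on.

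**Working it through.** **The plan's own figure.** The sample size section {14} gives 70 per group with 10% attrition, alpha 0.05 and 80% power (written there as beta). It gives no difference or SD, so 70 cannot be reproduced from stated inputs. It is consistent with an assumed standardised difference d = 0.5, two-sided: n = 2(1.96 + 0.842)²/0.5² = 62.8, rounded up to 63, and 63/0.9 = 70. That calculation concerns the two PD groups and is not in dispute. I borrow n = 63 and d = 0.5 to scale the PD-versus-healthy comparison.

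**Assumptions, none of them given in the protocol.**
- 63 analysed per group, unit variance, d = 0.5.
- 50 of the 63 healthy controls (about 80%) are spouses. PD participants are allocated 1:1, so about k = 25 couples link the healthy group to each PD arm.
- Within-couple correlation rho is varied from -0.2 to 0.5.

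**Formulas** for one PD arm versus healthy controls, N = 63 each:
- Variance assumed by the t test: 2/N = 2/63 = 0.03175.
- True variance of the mean difference: 2/N - 2·k·rho/N². The ratio of true to assumed is R = 1 - k·rho/N.
- True two-sided type I error: 2[1 - Φ(1.96/√R)].
- Power of the named test: Φ[(0.5/√0.03175 - 1.96)/√R].
- Variance for an analysis that uses the couples and keeps singletons: 2/(N - k + k/(1 - rho)). Its power is Φ(0.5/√variance - 1.96).

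**Example at rho = 0.5.** R = 1 - 25 × 0.5/63 = 0.802. The effective critical value is 1.96/√0.802 = 2.19, so the type I error is 2.9%. The couple-aware variance is 2/(38 + 50) = 0.02273, against 0.03175 assumed by the t test.

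| Couples per arm | rho | R | True type I error | Power, two-sample t | Power, couple-aware |
|---|---|---|---|---|---|
| 25 | 0.5 | 0.802 | 2.9% | 82.8% | 91.3% |
| 25 | 0.3 | 0.881 | 3.7% | 81.6% | 85.9% |
| 25 | 0.05 | 0.980 | 4.8% | 80.4% | 80.9% |
| 25 | -0.2 | 1.079 | 5.9% | (test too liberal) | – |
| 13 | 0.3 | 0.938 | 4.3% | 80.9% | 83.3% |

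The last row has about 40% spouses (26 of 63), a share that the eligibility section makes plausible.

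A simulation of the two-sample t test (40,000 runs, 63 per group, half of each group in couples) gave a type I error of 3.3% at rho 0.3 and 2.4% at rho 0.5. The formula with k = 31.5 gives 3.35% and 2.36%.

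**Pooled PD (126) versus healthy (63).** R = 1 - 2·g·rho/3, where g is the spouse share of the healthy group. For g = 0.7 to 1.0 and rho 0.1 to 0.3, the t test's standard error is 2% to 12% too large and the true type I error runs from 4.5% down to 2.8%.

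**The case against.** The strongest reply is that the share of couples is unknown and may be small. The comparator sentence can be read so that its adverb covers spouses and demographically similar people together, and two other sections make spouses an extra source. This stands: the size of the effect is conditional, and the 13-couple row shows how it shrinks.

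Second, a reader might infer that the trial planned a gain in precision from spouses and then threw it away. The documents do not support that. The comparator section says only that spouses may help, quantifies nothing, and can equally be read as making the groups comparable in lifestyle, a benefit that an unpaired comparison keeps. The sample size takes no credit for it.

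Third, a reader might infer that false positives are likely or that the trial's main result is at risk. Neither follows. Under positive correlation the test is conservative, and in every positive case above it keeps more than 80% power at d = 0.5. The randomised contrast is untouched.

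Fourth, this is a condensed article, and modelling detail may sit in an analysis plan. That would answer a complaint of silence, but the article does name a test, and its independence assumption conflicts with the recruitment it describes. Filing data by trial number does not show that the couple link is lost. The consent section {26a} describes a list of eligible participants and their spouses, so the link is known at recruitment. It remains to carry it into the analysis data.

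Finally, the type of t test for fNIRS is not stated, so the point is established only for tapping and neuropsychological outcomes.

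**Conclusion.** The point holds in a limited form. The named two-sample t test does not fit a healthy control group that contains spouses of PD participants, so PD-versus-healthy standard errors for tapping and neuropsychological outcomes are mis-stated whenever within-couple correlation is not zero.

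With 63 per group and 25 couples per arm, positive correlation of 0.3 to 0.5 takes the true type I error to about 3.7% to 2.9% and costs about 4 to 8 points of power at d = 0.5. A correlation of -0.2 raises the error to about 5.9%. At a correlation of 0.05 the power cost is under 1 point. These sizes rest on an assumed correlation, spouse share and effect size. The mismatch itself rests on the protocol's text. It is worth correcting because the remedy is cheap, but it does not threaten the comparison of PD intervention with PD control.

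**What to change.** Keep a coded couple identifier for each healthy control who is a participant's spouse. For PD-versus-healthy comparisons of tapping and neuropsychological outcomes, replace the two-sample t test with a linear mixed model that has group as a fixed effect and a within-couple covariance allowed to be positive or negative. A random couple intercept alone would force it to be non-negative. Unpaired PD participants and non-spouse controls stay in as singletons. A plain paired t test would not fit, because spouses are split across two PD arms and some controls have no partner in the trial.

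Use the same approach for subject-level fNIRS contrasts if healthy controls are compared with PD groups there. Age and gender adjustment is optional. It would also help to reconcile the comparator and eligibility sections on how far the healthy group will consist of spouses.

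The cost is one data field handled under the de-identification rule, one sentence of analysis wording, and one or two extra covariance parameters. No extra participants or visits are needed, and the analysis of the two randomised PD arms does not change.
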